### 5.6 Data collection

We will invite participants in both the intervention and control arms to visit the village clinics to receive a comprehensive survey and standard anthropometric measures at baseline and the end of the study (12 months). The data collection will be conducted following a standard protocol by trained staff recruited from the Center of Disease Control and Prevention (CDC) of a nearby county, who are completely blinded of randomized allocation of villages and will not be involved in the implementation of the intervention. For patients, a brief interviewer-administered questionnaire (**Appendix A-3**) will be completed using Qualtrics, an online-survey platform, which is able to ensure the quality of data through setting the format and force response. The questionnaire will collect data on demographic information, disease history, medication use and adherence, lifestyle behaviors, and utilization of healthcare services including hospitalization. Patients will have a physical examination comprising of assessment of blood pressure, weight, height, waist circumference and the "Timed Up and Go" test.

Village doctors will be invited to complete a self-administered knowledge-attitude-practices questionnaire (**Appendix A-4**) including questions regarding their demographic characteristics and clinical practice experience. The survey consists of 6 questions regarding their knowledge on the secondary prevention of stroke guidelines and 17 questions regarding their attitude and practice in delivering the stroke secondary prevention to patients evaluated by using 5-Likert scale.

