## 7. STATISTICAL ANALYSIS PLAN

### 7.1 General analysis principles

#### 7.1.1 Participant population.

Patient-level outcome data will be used, and stratification and clustering will be taken into account in all analyses. The analysis population will consist of all enrolled participants who completed the baseline assessment. Missing follow-up measurements due to (1) death, (2) moving away from the study area, or (3) refusing to participate in the follow-up assessment will be accounted for in the analyses.

The analysis will use the intention-to-treat principle whereby all participant-level outcome data will be analyzed according to the arm to which the patient was allocated. Given the challenges of defining protocol violation in the context of a complex multi-component intervention like SINEMA, we will not perform per-protocol analyses but will instead summarize adherence to intervention components among intervention-arm participants and will summarize the frequency of visits to the village clinic in the control arm.

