## 7.2 Primary effectiveness analysis

The mixed effects framework will be used to model the primary outcome of short-term and long-term change in SBP with a random intercept for cluster (to account for the cluster randomized design) and fixed effects for township (to account for the stratified randomization procedure). More specifically, the primary outcome will be regressed on an indicator for treatment arm, baseline SBP, gender and age—in order to gain power—and indicator variables for township. Restricted maximum likelihood will be used together with the between–within method to calculate test degrees of freedom. Both methods have demonstrated good performance for binary outcomes and this good performance is expected for continuous outcomes, particularly when there are fewer than 40 clusters. For completeness, between-arm differences will also be presented based on the same model but with no adjustment for age and gender.

Baseline characteristics will be cross tabulated according to the randomized arm to visually check for appropriate balance and to provide an overview of the study population. If substantial baseline imbalance between the two arms is identified and the relevant variable is beyond the list of pre-specified variables for adjustment, additional sensitivity analyses adjusted for these imbalanced variables will be performed to ensure the robustness of the analysis.

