#### *Mortality*

Mortality, an exploratory outcome of the original trial, will be considered as a key primary outcome of interests for the follow-up assessment considering the relatively long follow-up period. Date and cause of deaths will be collected from multiple approaches as mentioned above.

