#### *(2) Functional dependence*

Many stroke patients suffer functional dependence post stroke. Functional independence is a key factor in stroke rehabilitation. We will measure the functional dependence using activities of daily living (ADL) and instrumental activities of daily living (IADL) scales. ADL and IADL are considered a primary functional status measure in stroke rehabilitation because of their relative objectivity, simplicity, and relevance to patients.

2236 (3) Grip strength test

2237 We also performed grip strength tests for both hands among participants. The measurement was taken  
 2238 by using grip strength tools (Yuejian™ WL-1000, Nantong, China), which has been used in other studies  
 2239 previously as a standardized tool for grip strength assessment.

2240 **Table B-1. Schedule of assessments of SINEMA post-trial study**

| Aspect of data collection                                      | Baseline | 1-year follow-up | Post-trial follow-up |
|----------------------------------------------------------------|----------|------------------|----------------------|
| Questionnaire                                           |          |                  |                      |
| Demographics                                                   | √        | √                | √                    |
| Family information                                             | √        | √                | √                    |
| Lifestyle risk factors                                         | √        | √                | √                    |
| Disease history                                                | √        | √                | √                    |
| Cognitive function (CSI-D)                                     |          |                  | √                    |
| Disability (modified Rankin scale)                             | √        | √                | √                    |
| Functional dependence (ADL)                                    |          |                  | √                    |
| Health-related Quality of life (EQ-5D-5L)                      | √        | √                | √                    |
| Depression (PHQ-2 and PHQ-9)                                   | √        | √                | √                    |
| Medication adherence (4 item4-item Morisky Green Levine Scale) | √        | √                | √                    |

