### 3.4.2 Analysis of mortality

The follow-up period for mortality is from date of baseline to date of death, or the date of follow-up assessment, whichever came first. For missing information on date of death, we will use the following strategies: (1) For participants who died during the baseline and 12-month follow-up, we impute the date using the median survival time of deceased participants at 12-months; (2) For participants who died during the 12-month follow-up and post-trial follow-up, we will impute the date using the median survival time of deceased participants who died during the post-trial period.

The cause of deaths will be classified by adopting the classification for cardiovascular mortality and stroke-related mortality used by the Global Burden of Diseases, Injuries, and Risk Factors Study. For missing information on cause of death, deaths will be classified as other causes of deaths.

Mortality rate for each mortality outcome will be estimated as the number of events divided by the total person-months since baseline. We will assess cumulative incidence of all mortality outcomes with the Kaplan-Meier curves, while accounting for village as clustering. Cox proportional hazards models using the generalized estimating equation (GEE) approach with an independence working correlation and robust sandwich variance will be used to compute hazard ratios (HRs) and 95% confidence interval (95% CIs) for the analysis with events and date of death as dependent variable. Age, sex, and township will be adjusted when estimating HRs. We will test adherence to proportional hazards assumption by plotting smoothed Schoenfeld residuals.

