#### 3.4.4 Sensitivity analyses

Following the previous statistical analysis plan, sensitivity analyses will be performed involved additional adjustment for covariates that were statistically imbalanced between arms at baseline, associated with the status of loss to follow-up, or both, as well as include all outliers.

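### The main mortality model in Part B omits baseline modified Rankin score, which is scheduled for all participants, and so forgoes some power (about 0 to 9 points under assumptions not in the documents); the planned test itself is valid.

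*Combined protocol and SAP*

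**What the plan says.** Part B section 3.3.1 changes the rank of death: "Mortality, an exploratory outcome of the original trial, will be considered as a key primary outcome of interests for the follow-up assessment". Section 3.4.2 analyses it with "Cox proportional hazards models using the generalized estimating equation (GEE) approach with an independence working correlation and robust sandwich variance", and the covariates are stated in one sentence: "Age, sex, and township will be adjusted when estimating HRs". The subgroup paragraph in 3.4.3 itself describes this primary model as minimally adjusted.

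Baseline mRS is available. Table B-1 has a row "Disability (modified Rankin scale") ticked at baseline, one year and post-trial, and the scale is in the Part A baseline questionnaire (Appendix A-3). Part A section 5.6 says the electronic form is one "which is able to ensure the quality of data through setting the format and force response", and section 7.1.1 states: "The analysis population will consist of all enrolled participants who completed the baseline assessment". No count of completed mRS scores is given, so the documents support *scheduled for all*, not *recorded for all*.

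Baseline disability enters the mortality analysis in one place. Section 3.4.3 splits it into moderate-to-severe versus none-to-slight, and adds it with its interaction with arm.

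Section 3.4.4 plans sensitivity analyses with "additional adjustment for covariates that were statistically imbalanced between arms at baseline", and also for covariates associated with loss to follow-up.

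The plan's own reason for covariates is in Part A section 7.2, where baseline SBP, gender and age enter the SBP model "in order to gain power".

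**The concern.** Every other Part B outcome in 3.4.1 is adjusted for its own baseline value as well as age and sex. Death has no baseline value, and nothing prognostic takes its place. In stroke survivors, disability is a natural candidate for a strong predictor of death. It is already collected, and the authors thought it relevant enough to make it a mortality subgroup.

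At stake are some power for a key primary outcome, for which the documents state no power, expected deaths or target HR, and a reported HR that carries whatever disability difference arose by chance between two sets of 25 villages. Randomization was stratified by township only. The number of participants is fixed, so covariate adjustment is one of the few means left to improve this analysis.

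**Working it through.** **1. The plan's only power figure.** Part A section 5.3 gives 83% for SBP. Inputs: 23 villages per arm and 24 patients per village after losses, ICC 0.04, SD 20 mmHg, difference 5 mmHg, two-sided 5%.
- Design effect = 1 + (24 − 1) × 0.04 = 1.92.
- Effective n per arm = 23 × 24 / 1.92 = 287.5.
- SE = 20 × √(2/287.5) = 1.67, so 5/SE = 3.00.
- Noncentral t power = 0.834 (44 df) or 0.833 (40 df).

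The 83% reproduces. It says nothing about mortality.

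**2. Power with and without mRS, mRS not clustered by village.** Simulation of 2,000 trials per setting: 50 villages of 25, allocation stratified by township, Cox model with village sandwich variance, fitted with age, sex and township and then with mRS added. Assumed, not in the documents: HR 0.7 or 0.8; about 200 or 300 deaths; mRS 0 to 4 in shares 10/30/30/20/10%; mRS–age correlation 0.2; village log-hazard SD 0.15.

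| mRS effect on hazard | Gain in power (points) |
|---|---|
| 1.0 per grade | −0.3 to 0.1 |
| 1.2 per grade | −0.2 to 0.9 |
| 1.4 per grade | 1.3 to 1.9 |
| 1.7 per grade | 2.9 to 4.7 |
| 2.0 per grade | 4.9 to 8.5 |
| 1.5 for mRS ≥3 v <3 | −0.3 to 1.1 |
| 2.0 for mRS ≥3 v <3 | 0.8 to 2.2 |
| 3.0 for mRS ≥3 v <3 | 2.1 to 4.0 |

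**3. Power with mRS clustered by village.** A separate simulation: 1,500 trials per setting, 50 × 25, HR 0.72, about 270 to 285 deaths, sandwich variance × 50/44, t with 44 df.

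| HR per grade | Village ICC of mRS | Power without mRS | Power with mRS | Gain |
|---|---|---|---|---|
| 1.2 | 0.05 | 70.1% | 70.3% | 0.2 |
| 1.35 | 0 | 68.7% | 70.5% | 1.8 |
| 1.35 | 0.05 | 68.5% | 71.0% | 2.5 |
| 1.65 | 0 | 68.5% | 73.1% | 4.6 |
| 1.65 | 0.05 | 64.7% | 72.6% | 7.9 |

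A third set (villages of 26, 600 to 800 trials per setting, HR 0.72, the same 1.35 to 1.65 and ICC 0 to 0.05) gave gains from 2.3 points (63.5% to 65.8%) to 8.7 points (65.8% to 74.5%).

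**4. Where the gain comes from.** In the strongest unclustered case (HR 0.7, about 300 deaths, 2.0 per grade) the estimated HR was 0.723 without mRS and 0.695 with it, and the SE was 0.115 and 0.116.
- Without mRS: ln(0.723)/0.115 = −2.82.
- With mRS: ln(0.695)/0.116 = −3.14.

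The SE does not fall; the log HR lies further from 0. With mRS clustered (ICC 0.05, 1.65 per grade) the SE also falls a little, from 0.130 to 0.127.

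**5. Validity.** With a true HR of 1, rejection without and with mRS was 7.7% and 7.7% (1.4 per grade) and 6.9% and 7.2% (2.0 per grade). Both exceed 5% because the sandwich variance in step 2 had no correction for the number of villages. Leaving out mRS makes no material difference.

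**6. Chance imbalance.** The simulated SD of the arm difference in mean mRS was 0.097 grade at ICC 0.05 with 26 per village. At ICC 0 it is 0.097/√(1 + 25 × 0.05) = 0.097/1.5 = 0.065. Shift in log HR (95% range) = 1.96 × SD × ln(HR per grade), with ln 1.35 = 0.30 and ln 1.65 = 0.50.
- ICC 0: 1.96 × 0.065 × 0.30 = 0.038; × 0.50 in place of 0.30 = 0.064.
- ICC 0.05: 1.96 × 0.097 × 0.30 = 0.057; × 0.50 = 0.095.

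This is roughly 4 to 10% either way. The formula ignores age and township in the planned model. In step 3, which includes them, adding mRS moved the log HR with SD 0.031 and 0.051 at ICC 0.05, giving 1.96 × 0.031 = 0.061 and 1.96 × 0.051 = 0.100. At 2.0 per grade without clustering the SD was 0.055 to 0.057, so the shift would be slightly larger.

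**The case against.** The planned covariates are prespecified and match the age, gender and township set of Part A section 7.2. The HR is valid in a randomized comparison, and a minimally adjusted primary model is a legitimate choice. The gain in power comes largely from estimating an HR conditional on mRS. Every input to the power figures is assumed, and eligibility narrows the mRS range by excluding bedridden patients. All of this stands. It limits the size of the point but does not remove it.

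Four stronger readings are tempting and are not supported:

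- *The mortality HR is biased.* It is not. Chance imbalance averages to zero over randomizations and is part of the sampling variation that the planned interval already covers. It does shift the one HR that will be reported.
- *The trial loses 2 to 9 points of power.* No document figure supports this. The range is about 0 to 9, about 0 to 1 at 1.2 per grade, and about 0 to 4 if mRS is dichotomized as in 3.4.3.
- *A chance imbalance test is the only route for other covariates.* Section 3.4.4 has a second trigger, association with loss to follow-up, and 3.4.3 fits disability with an interaction. Neither fills the gap. Section 3.2.3 defines loss as known alive but not assessed, whereas deaths come from the registry, village doctors and verbal autopsy (3.2.2), so that trigger picks predictors of missing the survey. The subgroup model yields HRs by disability stratum, not an overall adjusted HR.
- *The imbalance test would flag about 16% of balanced variables.* This needs an unclustered test with the SBP ICC. The plan does not specify that test, and Part A section 7.1.1 says that clustering is taken into account in all analyses.

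**Conclusion.** The point holds as a missed opportunity in a key primary analysis, not as an error of validity. Leaving baseline mRS out of the 3.4.2 model forgoes about 0 to 9 points of power: roughly 2 to 8 if the hazard rises 1.35- to 1.65-fold per grade, and near 0 if mRS is weakly prognostic. The benefit is mainly less attenuation of the HR toward 1, with a small SE reduction if mRS clusters by village. On the 1.35 to 1.65 assumption, with a village ICC of 0 to 0.05, chance mRS imbalance can move the reported HR by roughly 4 to 10% (95% range). Death rates, target HR, mRS distribution, its effect and its clustering are all assumptions. Section 3.4.4 leaves the primary estimate unchanged, and its triggers do not select on prognosis for death. The change is worth making because it is cheap; the trial does not fail without it.

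**What to change.** In 3.4.2, add baseline mRS to the main Cox model for every mortality outcome, in one stated form (for example linear by grade), and report the age-sex-township model beside it. Fix this before post-trial deaths are compared by arm. Part B is dated August 2022 and 12-month mortality was already a planned between-arm comparison in Part A, so prespecification can be fully clean only for the post-trial deaths, and the text should say so. State how a missing mRS would be handled, since no completeness figure is given.

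For the mortality sensitivity analysis in 3.4.4, replace selection by an imbalance test with a short prespecified list of prognostic covariates.

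The cost is a few sentences of SAP text and one extra row of results. The small downside is that the HR becomes conditional on mRS and lies slightly further from 1 (about −0.33 against −0.31 on the log scale in the third set of simulations). Reporting both models makes that visible.

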### 3.4.3 Subgroup analyses

The subgroup analysis will be conducted by following the published statistical analysis plan to include subgroup analysis on gender (male/female), age group (<65 vs. ≥65), education level (schooling vs. no schooling), type of stroke (hemorrhage vs. ischemic stroke), years since last stroke events (less than 3 years vs. more than 3 years), and having benefit package for Chronic Diseases Outpatients (have benefit package vs. does not have the benefit package), Patient Health Questionnaire (PHQ-2) score (0-2 vs. 3-6). We will also conduct additional subgroups by marital status (married vs. widowed, divorced, or not married), annual household income (<5,000 vs. ≥5,000), years since the first stroke events (less than 5 years vs. more than 5 years), disability status (moderate to severe disability vs. no to slight disability). These subgroup analyses will be performed by adding to the model both the variable and its interaction term with treatment arm. We caution that these analyses may be not powered.

For mortality analysis, subgroup analyses will be conducted following the subgroups prespecified for the one-year outcome analysis. Additional subgroup analyses by considering

the baseline status of annual income (<5,000 vs. ≥5,000), marital status (married vs. widowed, divorced, or not married), systolic blood pressure (≥ 140 mm Hg vs. < 140 mm Hg), and disability status (moderate to severe disability vs. non-disability to slight disability) will also be conducted. Subgroup variable and its interaction term with the intervention were added to the minimally adjusted model used in the primary analysis as fixed effects in the subgroup analysis.

#### 3.4.4 Sensitivity analyses

Following the previous statistical analysis plan, sensitivity analyses will be performed involved additional adjustment for covariates that were statistically imbalanced between arms at baseline, associated with the status of loss to follow-up, or both, as well as include all outliers.

### 3.5 Data collection among village doctors

In addition to patient surveys, we will collect some basic information on all VDs in 50 villages who were part of the study. The survey will be designed on the basis of the survey from baseline and 12-month follow-up and a link of the survey will be sent to all VDs. The survey includes questions about their demographic information, history of medical training or education, current occupation, etc. They will also be asked about their knowledge, attitude and behaviors regarding the secondary prevention of stroke. This present follow-up for VDs is consistent with the procedure in previous protocol.

### 3.5 Qualitative assessment

Semi-structured in-depth interviews will be conducted for post-trial (**Appendix B-3**). The interviews would focus on how the SINEMA intervention effects lasted for long-term, and the potential enablers and barriers that may influence the sustainability. And we would explore the intervention components which got maintenance and may explain the mechanism of the sustainability of SINEMA intervention. The interviews will be conducted by the research teams. We will invite participants and stakeholders (including patients who suffered stroke, village doctors, physicians at township hospitals, and a county coordinator) to participate in the interviews.

We will use purposive sampling to ensure the diversity of the participants and the coverage across villages and townships. The research team will identify the villages to ensure that at least one village from each township would be selected. All intervention villages will be covered. Within each village, the research team will interview the village doctor and selected one or two participants based on their availability, willingness, ability to communicate, and demographic characteristics to ensure representatives of the participants. Interviews will be conducted either in the village clinics or at the homes of the participants. The physicians at township hospitals and the county coordinator who involved in the study will also be interviewed at their working places. All interviews will last between 20 and 40 min and will be audio-recorded with verbatim transcripts for data analysis.

## 4. QUALITY CONTROL AND PROJECT MANAGEMENT

### 4.1 Pilot study

To test the feasibility, reliability, and validity of the updated questionnaire and its procedure before the main trial, we will choose about 10 participants from one village to conduct the pilot testing of the questionnaire and procedure of data collection.

### 4.2 Project Management

The follow-up assessment was conducted under the management of the teams at Duke Kunshan University and Peking Union Medical College. The research teams will have weekly meetings to ensure the project will be ongoing as planned. The data collection will be administered with collaboration of Center of Disease Prevention and Control at Nanhe County and Ren County. To ensure the quality of assessment, a project coordinator will work with the data collector team.

The international steering committee and data management committee will continue their role in supervise and auditing the project.

